## Statistical analysis

5

In this study, we will conduct an analysis of the data utilizing the principles of modified intention-to-treat (ITT) analysis, which will encompass patients who have completed a baseline assessment of the primary outcome indicators. Safety analyses will be performed on all patients who have received at least one session of TMS. Continuous variables will be expressed as the mean ± standard deviation (SD) or median (25th percentile, 75th percentile), while categorical variables will be presented as percentages (%). For the assessment of baseline characteristics, continuous variables will be analyzed using One-way ANOVA (normal distribution) and Kruskal-Wallis H test (non-Gaussian distributions). Categorical variables will be evaluated using Chi-square or Fisher’s exact tests. The primary outcome measure will be the mean change from baseline over a period of 4 weeks, assessed at days 1, 5, 10, D10-24 h, then at weeks 1, 2, 3, and 4, specifically focusing on the average tremor score derived from the TETRAS. We will employ generalized estimating equations (GEE) for repeated measures within the modified ITT population. Additionally, sensitivity analyses will be conducted on the primary outcome, considering age, sex, disease duration, and baseline tremor score as covariates. Effects will be expressed as estimates along with 95% confidence intervals (CIs). GEE will also be applied to analyze secondary outcome measures, including the mean change in tremor power, amplitude, and frequency as recorded by accelerometers.

For data that is randomly missing between TMS sessions, where the missing data constitutes less than 5% of the sample, we will employ the last observation carried forward method to impute the missing values. Additionally, sensitivity analyses will be conducted to evaluate the impact of these imputations on the study outcomes. Conversely, missing data resulting from early dropouts (before 4 weeks) will not be imputed, as this data is not considered to be missing at random. Instead, these instances of missing data will be censored at the date of the participant’s last visit. All statistical analyses will be performed using IBM SPSS version 27.0, and *p*-values less than 0.05 will be considered statistically significant (two-tailed).

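### Early dropout is declared not missing at random and for that reason left unaddressed; the rule runs against its own premise, and no sensitivity analysis covers dropouts

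*Protocol article*

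**What the plan says.** The Statistical analysis section (section 5) of the protocol article fixes the following.

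- **Primary model:** "We will employ generalized estimating equations (GEE) for repeated measures within the modified ITT population". No weighting is stated. The modified ITT set is everyone with a baseline assessment of the primary outcome.
- **Gaps during treatment:** the rule is limited to sporadic gaps that the plan regards as random and that stay under 5%. The method for them is LOCF: "we will employ the last observation carried forward method to impute the missing values". A check on this step is promised: "sensitivity analyses will be conducted to evaluate the impact of these imputations on the study outcomes".
- **Early dropout:** the rule and its reason are given together: "missing data resulting from early dropouts (before 4 weeks) will not be imputed, as this data is not considered to be missing at random". What the plan does in place of imputation is to cut these patients off at the point where they were last seen; its word for this is censoring.
- **Other sensitivity analysis of the primary outcome:** "sensitivity analyses will be conducted on the primary outcome, considering age, sex, disease duration, and baseline tremor score as covariates".

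The primary outcome (section 2.7.1) is the mean change in TETRAS from baseline over eight post-baseline visits: D1, D5, D10, D10-24 h and W1 to W4. The target is eight patients per group (section 2.8).

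**The concern.** The plan gives a belief about dropout as its reason for doing nothing about dropout. If patients leave for reasons tied to scores that are never seen, those who remain at later visits no longer represent their arm. An analysis of the observed visits alone then estimates the wrong contrast at those visits. Declining to impute does not avoid an assumption. It assumes that the dropout mechanism can be ignored, which is what the plan has just denied.

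Censoring at the last visit belongs to time-to-event analysis. For a repeated score it means only that the later values are absent.

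Imputation is meanwhile used where it is least needed. Values missing at random within the treatment course can be handled by a repeated-measures model without filling. LOCF instead enters an earlier score at a later visit and treats it as observed.

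At stake are the W1 to W4 contributions to the primary mean. With eight per arm, one or two losses are 1/8 = 12.5% to 2/8 = 25% of an arm. Section 2.8 says the results will inform the sample size of a Phase 3 trial.

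**Working it through.** **No figure to reproduce.** The sample size is taken from earlier pilot studies, and the article states no effect size, SD, power or dropout rate. The check is therefore a comparison of the text with itself, followed by an illustration on stated assumptions.

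**1. The rules side by side**

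| Missing data | Plan's belief | Plan's handling | Sensitivity analysis named |
|---|---|---|---|
| Gaps between TMS sessions, under 5% | random | LOCF | yes, for these imputations |
| Dropout before 4 weeks | not at random | not imputed, censored | none |

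The covariate-adjusted analysis does not vary any assumption about missing scores. The data called non-random therefore have no sensitivity analysis.

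**2. Illustration A: a true difference exists**

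Assumptions, none from the documents:
- 20,000 per arm (to show bias, not sampling error) and 8 visits;
- SD 1, within-patient correlation 0.6, true dual-minus-sham difference 0.80 SD at every visit;
- dropout from W1 onward, with probability 0.3 or 0.5 at each visit when the change score is worse than a cut-off of 0.5 SD;
- the score that triggers dropout is the previous one (missing at random, MAR) or the current unseen one (not at random, MNAR).

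This gives dropout of 29-41% in sham and 10-15% in dual.

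| Analysis | Eight-visit mean | W4 |
|---|---|---|
| Independence GEE, MAR or MNAR | 0.72-0.77 | 0.55-0.66 |
| Correct exchangeable GEE or mixed model, MAR | about 0.80 | about 0.80 |
| Correct exchangeable GEE or mixed model, MNAR | not tabulated | 0.73-0.77 |

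Shortfall for independence GEE:
- Eight-visit mean: 0.80 - 0.77 = 0.03 to 0.80 - 0.72 = 0.08 SD, or 0.03/0.80 = 4% to 0.08/0.80 = 10%.
- W4: 0.80 - 0.66 = 0.14 to 0.80 - 0.55 = 0.25 SD, or 0.14/0.80 = 18% to 0.25/0.80 = 31%.

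**3. Illustration B: no true difference, informative loss in the active arm**

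Assumptions: 4,000 per arm, correlation 0.6, about 22-26% dropout in each arm. Active-arm dropout depends on poor scores; control-arm dropout is completely at random (MCAR). Entries are bias in SD units, eight-visit mean / W4; negative values favour the active arm.

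| Active-arm mechanism | Independence GEE | Exchangeable GEE |
|---|---|---|
| MCAR | -0.006 / -0.014 | -0.011 / -0.027 |
| MAR | -0.083 / -0.194 | -0.014 / -0.017 |
| MNAR | -0.085 / -0.222 | -0.025 / -0.072 |

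In A the bias shrinks a real effect; in B it creates a false one. In both, modelling the correlation removes most of the bias under MAR and leaves some under MNAR.

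**4. Scale against sampling error**

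For a mean of eight visits with correlation 0.6, the variance factor is (1 + 7 x 0.6)/8 = 0.65. With eight per arm, the standard error of the contrast is sqrt((2/8) x 0.65) = 0.40 SD. A bias of 0.03-0.08 SD is 0.03/0.40 = 0.08 to 0.08/0.40 = 0.20 of one standard error.

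**5. Scale of LOCF**

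The 5% limit is 0.05 x 24 x 8 = 9.6 of 192 scores; 0.05 x 24 x 3 = 3.6 of 72 scores at D1, D5 and D10; or 0.05 x 24 = 1.2 of 24 patients. On any of these readings it touches little data.

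**The case against.** The strongest reply has five parts.

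- **GEE is not the culprit.** A reader might infer that GEE is valid only if data are missing completely at random, and that a mixed model would put this right. That is too strong. The large losses come from an independence working correlation, and the article names none, which it may leave to the analysis plan. With a correct exchangeable correlation, GEE and the mixed model agree: about 0.80 under MAR, and both short at W4 under MNAR. This stands, so changing the model is not by itself the remedy.
- **Dropouts are not discarded.** Scores up to the last visit remain in the modified ITT analysis. This stands; only the later visits are absent.
- **The bias in the primary endpoint is small.** It is at most about a fifth of a standard error in Illustration A, and W4 alone is not a named endpoint. This stands and limits the severity.
- **The dropout pattern is invented.** A reader might infer that non-improvers leave sham and that the late effect is understated. The documents do not support that. Patients are blinded, all groups are offered later open-label stimulation (section 2.3.3), and the Discussion cites improvement under both real and sham stimulation. Section 2.6 lists adverse events among the reasons to end the intervention, which could equally remove active-arm patients. This stands: neither rate nor direction is known.
- **LOCF is contained.** It is capped below 5% and has its own sensitivity check. This stands; it is a poor choice with little reach.

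None of this touches the dropout rule. An analysis plan not shown here could add a dropout sensitivity analysis, but it would inherit the stated rule and its stated reason.

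**Conclusion.** The point holds and should be fixed. The plan assumes that dropout is not at random, then handles it in a way that is not valid under that assumption, offers a censoring device with no function for a repeated score, and names no sensitivity analysis for those patients. This is a stated rule with an unsound reason, not a detail left for later.

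On the assumed rates, the effect on the eight-visit primary mean is modest, about 0.03-0.08 SD out of 0.80 with an independence working correlation. It is larger at W4, about 0.14-0.25 SD. With the correlation correctly modelled, the bias essentially disappears under MAR, but W4 is still short by 0.03-0.07 SD (0.80 - 0.77 to 0.80 - 0.73) under MNAR, the mechanism the plan believes in. All these figures rest on assumed dropout rates, correlation and triggers, and the direction can reverse. The documents do not support a claim that the trial's result will be biased by a given amount or in a given direction.

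**What to change.** Change the Statistical analysis section in three places.

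1. Delete the LOCF rule and the censoring rule, together with the rationale that links no imputation to not missing at random.
2. Analyse all observed scores with a likelihood-based repeated-measures model. A GEE would also serve, with a stated non-independence working correlation or inverse-probability weights.
3. Because the plan believes that dropout is not at random, add one stated departure analysis for dropouts: either reference-based imputation from the sham trajectory, or a worsening shift increased until the conclusion changes. Step 2 alone does not answer that belief.

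The cost is analysis wording and one extra sensitivity run. No visits, patients or procedures are added. Recruitment was ongoing at submission (section 2.1), so the change should be made and dated before the data are unblinded.

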## Discussion

6

The objective of this study is to examine the safety, efficacy, and feasibility of dual-target TMS therapy for the treatment of ET. While this investigation will primarily function as a pilot study for a larger multicenter trial, it aims to explore novel therapeutic possibilities for ET.

Dual-target TMS shows great potential in the treatment of neurological diseases. A study exploring the efficacy of combined TMS targeting the cerebellum and the M1 in patients with tremor-dominant subtypes of Parkinson’s disease (T-PD) found that dual-target rTMS significantly outperformed single-target rTMS in alleviating tremor symptoms, enhancing quality of life. While this study focuses on T-PD, it also raises the potential application of dual-target rTMS to treat tremor symptoms in other contexts (48). Furthermore, dual-target TMS has been shown to be more effective than single-target stimulation in facilitating symptomatic improvement in conditions such as chronic tinnitus and post-stroke cognitive impairment (49, 50). Abnormalities in the CTC loop play a significant role in the pathogenesis of ET, dual-target TMS can simultaneously affect multiple nodes in the CTC circuit involved in ET, potentially achieving a more comprehensive therapeutic effect.

cTBS uses rapid pulse patterns to quickly inhibit targeted brain areas (51), while low-frequency rTMS provides more lasting effects, suitable for long-term modulation (52). We hypothesize that combining these TMS techniques can yield complementary benefits. Chuang et al. (32) found that cTBS suppresses motor cortex excitability in ET patients and reduces tremor amplitude. Batra et al. (33) showed that cTBS significantly improves tremor symptoms by increasing the contralateral silent period (cSP). Gironell et al. (25) and Popa et al. (29) reported tremor improvements after rTMS stimulation of the cerebellum. However, data on the effects of noninvasive brain stimulation techniques applied to the cerebellum and motor areas of ET patients show variability in their effects on tremor (53, 54). Specifically, there is a significant degree of variability among individuals. Olfati et al. (28) found no significant improvement in the overall tremor score with rTMS compared to sham stimulation on days 5, 12, or 30 after treatment. In contrast, Popa et al. (29), using the same stimulation protocol, observed a significant and lasting reduction in all aspects of tremor. It is important to consider that ET is a highly heterogeneous disorder with potential inter- and intra-individual differences, where factors such as anxiety (55), fatigue (56), and caffeine consumption (57) can all influence the severity of tremors. Furthermore, the placebo effect is a concern that should not be overlooked; Shin et al. (27) found that there was an improvement in tremor scale scores regardless of whether the stimuli were real or sham. The cerebellum and cortex are the most popular targets for stimulation in TMS studies aimed at treating ET. Previous findings suggest that the outcomes of TMS for ET are highly variable, and we speculate that the use of double-target stimulation may enhance the stability of treatment effects.

In this study, we will use Rs-fMRI to explore the alterations in brain functional connectivity before and after TMS treatment for ET, as well as to assess whether FC differs among three distinct groups. Studies have shown disruption in FC between the bilateral cerebellum and the cortex in patients with ET (58, 59). Furthermore, tremor severity may exhibit a positive correlation with FC between cerebellar lobule VI and VIM, as well as between the VIM and the cortex (60). These findings underscore the critical role of the CTC loop in the pathogenesis of ET.

Gironell et al. found a significant reduction in tremor scores 5 min after rTMS, but the effect disappeared 60 min after stimulation. Low-frequency rTMS may temporarily affect tremor production by modulating cerebellar output (25). Popa et al. found that cerebellar rTMS restored FC in the CTC network after five consecutive days of treatment (29). Previous studies have shown that patients with ET have increased tremor-related activity in several regions of the cerebellum (61). TMS applied to the cerebellum modulates synaptic plasticity and thus restores normal function of circuits involved in motor control in the cerebellum (62). While cTBS may reduce the excitability of the M1 cortex by inducing long duration depression (LTD), thereby decreasing tremor amplitude (33). Several studies have shown that ET is associated with abnormal function of the inhibitory neurotransmitter γ-Aminobutyric Acid (GABA) (32, 63, 64), GABA levels in the CSF have been observed to be decreased (65). Patients with ET exhibit heightened 11C-Flumazenil binding to GABA receptors within the ventrolateral thalamus, dentate nucleus, and pre-motor cortex (66). In our study, we will further explore the mechanism of TMS for ET using MRI.

It was found that cTBS applied to either the motor cortex or the cerebellum resulted in a reduction of MEP in healthy control subjects, but not in individuals with ET (30, 31). A potential explanation for this discrepancy is that the cerebellar-brain inhibition (CBI) may be altered in patients with ET. Following the administration of TMS to the cerebellum, if TMS is subsequently applied to the motor cortex within a 5–7 ms interval, a reduction in motor cortex-evoked MEPs is observed; this phenomenon is referred to as CBI (67), which is believed to be mediated by enhanced inhibition of Purkinje cell output to the dentate nucleus and thalamus (68). In addition, the cerebellum plays a central role in the pathogenesis of ET (69), we intend to first stimulate the cerebellum and subsequently the cortex to further investigate this mechanism from an imaging perspective.

In summary, TMS may serve as a valid tool for the treatment of ET and for modulating the CTC pathway, we use a combination of cortical and cerebellar stimulation, as suggested by evidence-based guidelines. Conducting a study on dual-target stimulation holds promise for improving patient outcomes. Furthermore, MRI has been utilized to investigate the pathogenic pathways associated with ET, providing insights into the underlying mechanisms of this condition. Such advancements have the potential to substantially enhance the quality of life for individuals affected by ET, enabling them to regain independence and participate in daily activities.
